**Image Acquisition**

Collected images will include structural images for functional data overlay, diffusion tensor images for correlating fiber tract integrity with craving scores, resting functional images for baseline connectivity effects, and task-evoked functional images for examining image-induced regional brain activation. All images acquisitions do not involve contrast and are minimal risk. 128 T1 volumetric 3-D SPGR whole-brain sagittal images will be acquired from all study participants at 3 T with a SENSE head coil. Parameters: Flip = 20 degrees, TE = 4.2 ms, slice thickness = 1.2 mm, no skip, field of view (FOV) = 24x 24 cm, matrix size 256 x 256 pixels for an in-plane resolution = 0.88 mm. Whole brain 3-D images will be used for overlay of functional data in 3-D space. We will acquire whole-brain functional oblique slices of 4.5 mm thick covering the regions of interest (TE=35 ms, TR=2 s, Flip=790, matrix 64 x64. Images will be collected on the 3.0 T Philips scanner using a quadrature head coil. We will collect whole-brain axial slices of 4.5 mm thick with 0.5 mm skip. We will analyze fMRI data using the Brain Voyager QX software (Brain Innovation, Maastricht, The Netherlands) or other analysis package employing the general linear model (GLM) to construct statistical parametric maps SPMs to examine regional brain activation in response to photic stimulation and the semantic task. Preprocessing: 3-D motion correction (runs having over 2 mm translational motion or more than 1 degree rotational motion will be excluded), spatial smoothing (4 mm FWHM Gaussian kernel), temporal smoothing (linear trend removal and 3-Hz high pass filtering) (Skudlarski et al., 1999). Statistical threshold for activation will be a false discovery rate of 0.05, corrected for the number of multiple independent whole-brain comparisons. The stimulus paradigm time courses will be convolved with a hemodynamic response gamma function (Boynton et al., 1996). Following SPM construction, activation within a desired region of interest will be determined as the number of pixels reaching statistical threshold and the percent BOLD signal change within the activated pixel region. The method for choosing ROI's is defined below.

1. **Risks**

This study will include adults (18-35 years old).

Potential Risks of fMRI Imaging:

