**General statistical methods**

Percent BOLD signal change in the targeted ROIs, as well as demographic characteristics of the experimental and control group will be summarized using descriptive statistics. Given proposed group sizes of 10 participants (with no missing data), we expect to use parametric statistical analysis procedures. However, samples of this size are highly sensitive to outlier values, thus visualization and statistical investigations of parametric assumptions will be conducted. Because relative (greater or lesser) differences in activation rather than absolute values of those differences are of primary interest in this research, if distributions do not meet parametric assumptions, depending on the nature of the violations methods based on ranks will be used or outliers will be dealt with on a case-by-case basis.

Assuming multivariate normality and homogeneity assumptions are met, multivariate profile analysis (Tabachnick & Fidell, 2000) will be used to investigate differential patterns of ROI activation (profiles) between the two primary study groups of cannabis users and non-user controls (Primary Specific Aim 1). A statistically significant interaction effect of study group and ROI (e.g., insula, inferior frontal cortex, ventrolateral prefrontal cortex, parahippocampal gyrus, bilateral fusiform gyrus) will indicate statistically significant differences in activation (% BOLD signal change) profiles. Given a statistically significant interaction effect from an overall profile analysis, post-hoc tests controlling the experiment-wise Type I error rate will be used to determine precisely which component members of the profile (i.e., areas of activation or ROIs) are contributing to the overall profile difference, as well as the magnitude and direction of the specific component difference. These effect sizes will be used for statistical powering estimates in the planning of subsequent RO1 research.

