**Power Estimates**

Because this is a pilot study to demonstrate feasibility, we estimate 10 subjects per group as reasonable sample size as this group size is commonly well in fMRI pilot studies. A key outcome of this study will be the calculation of effect sizes that will inform the powering of subsequent, larger studies. Commercially available statistical software packages (NCSS and PASS, number Cruncher Statistical Systems, Kaysville, Utah; SPSS, Chicago, IL; Stata, College Station, TX) will be used for data analysis.

1. **Privacy/Confidentiality Issues**

The participant research file will contain information concerning mental and physical health and experimentally derived data. All data collected in this study will be used specifically for research purposes. Should information that might have a bearing on the well being of participants be discovered, this information will be communicated to participants and, at the participant’s request, with their physician.

Electronic databases containing identifiable participant information will be password encoded. Written information containing participant identifiers (informed consent, lab results, participant payment, etc) will be stored in file cabinets in offices with the departments of Radiology and Psychiatry. Participants will be assigned an alphanumeric code that will be used to label all research data.

1. **Follow-up and Record Retention**

This pilot study is expected to last one year with data analysis continuing indefinitely. Records may be destroyed after data analysis is complete and all manuscripts are published, but records may be maintained indefinitely for future analysis. Emerging methods of analysis in fMRI research may permit the reanalysis of previously acquired data to extract new meaning.

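### ROI % BOLD change is taken only from voxels that passed the activation threshold in the same data, which inflates it and can distort the effect sizes the pilot is meant to deliver

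*Protocol*

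**What the plan says.** **How the ROI value is obtained.** Protocol, Image Acquisition, sets the cut-off: "Statistical threshold for activation will be a false discovery rate of 0.05, corrected for the number of multiple independent whole-brain comparisons". Once the maps are built, activation in an ROI is "the number of pixels reaching statistical threshold and the percent BOLD signal change within the activated pixel region". There are thus two measures, a count of passing pixels and a % BOLD change confined to those pixels. No separate localiser, split of runs or average over the whole ROI is described. The section adds "The method for choosing ROI's is defined below", but nothing later in the protocol defines it; General statistical methods only lists regions as examples.

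**Where the value goes.** General statistical methods summarises "Percent BOLD signal change in the targeted ROIs" and uses a group-by-ROI profile analysis, whose interaction is read as "statistically significant differences in activation (% BOLD signal change) profiles". The exercise comparison models activation within key ROIs by GEE. Effect sizes from both are to power the follow-on study, and Power Estimates states: "A key outcome of this study will be the calculation of effect sizes".

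**Missing values.** General statistical methods begins its choice of methods with "Given proposed group sizes of 10 participants (with no missing data), we expect to use parametric statistical analysis procedures".

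**The concern.** A voxel enters the ROI average only if its own estimate was large relative to its noise. Averaging those same estimates gives a figure that must lie above the cut-off, whatever the ROI's true response. Three consequences follow.

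- Absolute activation is overstated. A true difference between groups or exercise conditions can shrink, because both averages are pushed up towards or above the same cut-off.
- The cut-off on the % BOLD scale rises with scan noise. A noisier scan can therefore report a higher % BOLD from fewer voxels.
- With a threshold per participant, an ROI in which nothing passes has no % BOLD value, and it is missing because measured activation was low.

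The pilot's stated product is a set of effect sizes. If the variable behind them is distorted, the next study is sized on the wrong numbers.

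**Working it through.** **No figure to reproduce.** The 10 per group rests on custom for fMRI pilots, with no effect size, SD, alpha or power stated. The check therefore asks how the defined measure behaves.

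**Inputs from the protocol.** FDR 0.05; runs of 7 blocks x 30 s = 210 s; TR 2 s, so 105 volumes per run; 3 runs per exercise condition (it is unclear whether that means one or three per stimulus type); 10 per group.

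**Assumed, because the protocol does not give them.** Voxel standard error s, cut-off z, and true ROI means.

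**Step 1: truncated-normal model.** Voxel estimates are normal with mean mu and SE s, and are kept if above c = z x s. With a = z - mu/s:

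- reported mean = mu + s x phi(a) / [1 - Phi(a)]
- share of voxels passing = 1 - Phi(a)

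At z = 3.1, s = 0.15:

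- mu = 0.10: a = 2.433; 0.10 + 0.15 x 0.02066/0.00748 = 0.514
- mu = 0.30: a = 1.100; 0.30 + 0.15 x 0.2179/0.1357 = 0.541

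The reported difference is 0.027 against a true 0.20, a loss of 87%. Over a range of s (losses from unrounded values):

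| s | 0.10 reported as | 0.30 reported as | loss, 0.10 vs 0.30 | 0.60 reported as | loss, 0.30 vs 0.60 |
|---|---|---|---|---|---|
| 0.05 | 0.180 | 0.300 | 40% | 0.600 | 0% |
| 0.10 | 0.346 | 0.386 | 80% | 0.601 | 29% |
| 0.15 | 0.514 | 0.541 | 87% | 0.649 | 64% |
| 0.20 | 0.683 | 0.705 | 89% | 0.773 | 77% |

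At z = 2.6 and s = 0.15, the means 0.10 and 0.30 are reported as 0.447 and 0.482, a loss of 82%.

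**Step 2: same truth, different noise.** With mu = 0.20 and z = 3.1, raising s from 0.10 to 0.20 moves the reported value from 0.361 to 0.692, while the passing share falls from 13.6% to 1.8%.

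**Step 3: the pixel count.** At z = 3.1 and s = 0.15, the passing share is 0.7% for a true 0.10 and 13.6% for a true 0.30. The count still separates them, and it is 0, not undefined, when nothing passes.

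**Step 4: simulation with FDR applied directly.** A fixed z only approximates an FDR cut-off, which adapts to each map. The protocol's block design and TR were therefore simulated with a gamma response, a linear trend and Benjamini-Hochberg at 0.05. The SE of % BOLD per 1% temporal noise is 0.212 for one run and 0.212/sqrt(3) = 0.122 for three. Assumptions: temporal noise 1-2%, varying 10% or 25% between people; mean true response 0.1-0.5%, between-person SD 0.15 or 0.30; voxel SD 0.15 within the ROI; 60 ROI voxels of 20,000, independent; 2-10% of the brain active elsewhere; threshold per participant.

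- *Inflation:* a true 0.30 is reported as 0.51-0.56 (three runs, noise 1%), rising to about 1.4 (one run, noise 2%).
- *Noise versus truth:* thresholded % BOLD correlated more with a person's noise than with the true response in 34 of 36 scenarios of one grid and 36 of 48 of another, 70 of 84 in all. It reversed with three runs, low noise and strong or variable activation (for example r = 0.95 with truth, 0.06 with noise).
- *No voxel passing:* 0% to 95% of participant-ROIs across all scenarios. At true 0.30, noise 1% and between-person SD 0.15, it was about 10-25% with one run and 0.5-4% with three.
- *True group difference of 0.20 (0.2 vs 0.4), 10 per group:* the thresholded measure shows 0.05-0.10 and rejects in 7-26%. The whole-ROI mean shows 0.20 and rejects in 77-82%.
- *No true difference:* with equal noise, the thresholded test stays near 5%. With 25% more noise in one group it rejects in 8-36%; the whole-ROI mean stays at about 5%.

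**The case against.** **The level of thresholding is not stated.** The map could be individual or group. A pixel count used as an activation measure implies individual maps but does not prove it. A common group-map voxel set would weaken the noise and missing-value points. The values would still come from voxels chosen on the same data.

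**A reader might infer that the outcome measures noise rather than activation.** The protocol does not show that. It held in most assumed scenarios, not all; only the possibility is supported.

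**A reader might infer that the group test is itself circular.** It is not. Selection is on stimulus versus baseline, and with equal noise and equal truth the false-positive rate stays near 5%. False differences need unequal noise, which the protocol does not indicate. Excluding runs with more than 2 mm or 1 degree of motion limits such imbalance but does not ensure equality.

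**A reader might quote one loss figure.** The 87% belongs to one choice of SE and true means. With strong activation and low noise the loss is nil.

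**Other text in the plan helps somewhat.** Section 2.0 says the ROIs are set beforehand and keeps whole-brain analysis exploratory; analysts are blinded to group and exercise condition; relative differences matter more than absolute ones. None of this changes how the value is taken inside an ROI. Relative order is not safe either: in the table, a true 0.30 at SE 0.10 reads 0.386, and a true 0.10 at SE 0.15 reads 0.514. Masks and empty-ROI handling may sit in an analysis plan not shown, but the measurement rule is stated here.

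**The count survives.** This is true, but the profile analysis is specified on % BOLD.

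**A whole mask dilutes focal activation.** This also stands. If 20% of voxels respond at 0.5% vs 0.8% (assumed, SE 0.10), the thresholded mean gives 0.51 vs 0.80 and the whole-mask mean 0.10 vs 0.16.

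**It is a small pilot, and the images can be re-analysed.** That makes the change cheap. It does not make it unnecessary, since effect sizes are the product.

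**Conclusion.** The concern holds in a bounded form. The protocol fixes a rule under which ROI % BOLD is selected and measured on the same map, and nothing later replaces it. Absolute activation is inflated. True differences can be compressed: 40-89% for 0.10% vs 0.30% and 0-77% for 0.30% vs 0.60%, at z = 3.1 over voxel SE 0.05-0.20. The measure can track scan noise more than true activation. False group or condition differences arise only where noise differs between them.

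If thresholding is per participant, % BOLD (not the count) has no value in an ROI where no voxel passes, which conflicts with the assumption of complete data.

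The direction of the inflation follows from the stated rule. The sizes rest on assumed noise, true responses, a normal model and, for the simulation, independent voxels and per-participant thresholds; none of these can be checked from the protocol.

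**What to change.** - Name the ROIs as a closed list before analysis, replacing the example list and supplying the missing ROI method.
- Define the outcome for each ROI as the mean % BOLD change (GLM beta) over all voxels of a fixed anatomical mask, the same for every participant and exercise condition and independent of any activation threshold.
- Use that outcome in the profile analysis, the exercise model and the effect sizes for the later study.
- Keep the FDR maps for the exploratory whole-brain analysis, and report suprathreshold pixel counts descriptively.

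In the simulation, the whole-ROI mean was unbiased, correlated 0.91-0.99 with the true response and between -0.10 and 0.10 with noise, and was always defined.

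Cost: wording and standard masks, with no new data. Whole-mask means will be smaller and will dilute focal activation; small masks specified in advance would limit this.

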**General statistical methods**

Percent BOLD signal change in the targeted ROIs, as well as demographic characteristics of the experimental and control group will be summarized using descriptive statistics. Given proposed group sizes of 10 participants (with no missing data), we expect to use parametric statistical analysis procedures. However, samples of this size are highly sensitive to outlier values, thus visualization and statistical investigations of parametric assumptions will be conducted. Because relative (greater or lesser) differences in activation rather than absolute values of those differences are of primary interest in this research, if distributions do not meet parametric assumptions, depending on the nature of the violations methods based on ranks will be used or outliers will be dealt with on a case-by-case basis.

Assuming multivariate normality and homogeneity assumptions are met, multivariate profile analysis (Tabachnick & Fidell, 2000) will be used to investigate differential patterns of ROI activation (profiles) between the two primary study groups of cannabis users and non-user controls (Primary Specific Aim 1). A statistically significant interaction effect of study group and ROI (e.g., insula, inferior frontal cortex, ventrolateral prefrontal cortex, parahippocampal gyrus, bilateral fusiform gyrus) will indicate statistically significant differences in activation (% BOLD signal change) profiles. Given a statistically significant interaction effect from an overall profile analysis, post-hoc tests controlling the experiment-wise Type I error rate will be used to determine precisely which component members of the profile (i.e., areas of activation or ROIs) are contributing to the overall profile difference, as well as the magnitude and direction of the specific component difference. These effect sizes will be used for statistical powering estimates in the planning of subsequent RO1 research.

Graphical and descriptive statistical techniques will be used to explore patterns of changes in activation within subjects to cannabis cues after the two exercise conditions (Primary Specific Aim 2). Tests of the changes in activation within key ROIs will be conducted using general linear modeling (GLM) methods that incorporate Generalized Estimation Equations (GEE) for parameter estimation of correlated data. The combination of GLM and GEE provides the most flexibility for modeling data of uncertain distribution, as well as for incorporating the mixed effects of between (cannabis vs. control) and within (prior exercise state). Again, effect sizes generated from these analyses will be used for statistical powering of planned subsequent RO1 research.

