**2.0 Rationale and Specific Aims**

It is unknown how the response of cannabis users might compare to those of non-users in response to similar dose of physical activity. We will therefore compare brain activation during craving to cannabis, a natural reward (food) and a neutral scene (nature images). The food cues will allow us to determine if effects of exercise on brain activation and craving generalize to two different reward conditions and the nature scenes provide a neutral, no rewarding control. In addition to the analysis of predetermined regions of interest, whole-brain exploratory analyses will also be conducted to examine for additional brain regions showing associations between various conditions of interest and regional brain activation.

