**Specific Aims**

1. To explore methodological factors involved in finding the relationship between PA and cannabis use.
   1. to examine the effects of cannabis and food cues on brain activation and craving in cannabis users and nonusers
   2. to examine the effects of vigorous exercise on brain activation and craving in response to cannabis and food cues.

Our working hypothesis is that the regional brain activation in response to drug cues will be different in cannabis users than in controls and that exercise will significantly alter brain responses to these cues in both groups. Our secondary hypothesis is that exercise will tend to normalize the abnormal brain activation observed in cannabis users.

Our expectation is that exercise will alter cue-responding in terms of brain activation or craving. It is possible that exercise may be a useful treatment in cannabis dependence. Future studies may examine this specific relationship.

There are no reports available exploring the relationship between physical activity and cannabis use.

Current data suggest that there are convergent findings regardingthe chronic and acute effects of cannabis on brain activity

1. **Inclusion/Exclusion Criteria**

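### The only stated Aim 1 test, a group-by-ROI interaction that also gates the ROI-level tests, detects a user-control difference common to all ROIs only at the alpha rate, and no stated test uses the nature-scene control

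*Protocol*

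**What the plan says.** Specific Aims states the working hypothesis that "the regional brain activation in response to drug cues will be different in cannabis users than in controls". The first sub-aim is "to examine the effects of cannabis and food cues on brain activation and craving in cannabis users and nonusers".

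General statistical methods (Statistical Considerations) assigns Aim 1 to a multivariate profile analysis of percent BOLD change in the ROIs, users against controls. The criterion it names is "A statistically significant interaction effect of study group and ROI". It continues: "Given a statistically significant interaction effect from an overall profile analysis, post-hoc tests controlling the experiment-wise Type I error rate will be used". The effect sizes for the planned larger study are said to come from this step. The paragraph names no overall group (levels) test, no cue and no contrast between cues.

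The paragraph on Aim 2 plans GLM/GEE models of activation to cannabis cues within key ROIs, with group and prior exercise state as factors. It does not mention nature scenes.

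On the control condition, section 2.0 says that "the nature scenes provide a neutral, no rewarding control" and that activation will be compared across cannabis, food and neutral images. Stimuli plans separate nature runs, sets the food cues against nature, and uses blurred images as the baseline within each run.

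**The concern.** A group-by-ROI interaction depends only on differences between ROIs. If users respond more (or less) than controls by a similar amount in every ROI, the profiles are parallel and the interaction is null. The hypothesis in Specific Aims covers that pattern, and the Background subsection on regions of interest makes it plausible: it describes activity as generally raised during exposure and generally lowered during abstinence across several regions. Followed as written, the rule would then report no profile difference and would not go on to the ROI tests. Power Estimates calls the calculation of effect sizes a key outcome of the study, so the gate bears on the main product of the pilot.

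The second strand is cue specificity. Neither stated test contrasts cannabis or food images with nature images, so a group difference that is not specific to the cue is not separated from a drug-cue response.

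**Working it through.** The protocol gives no power, effect size or SD for this test, so there is no figure of its own to reproduce.

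**Inputs from the protocol.** 10 per group with no missing data (General statistical methods); five ROIs, listed there as examples.

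**Assumptions.** SD 1 in each ROI; equal between-ROI correlation ρ of 0.3, 0.5 or 0.7; two-sided alpha 0.05 for the group test (the protocol states 0.05 only as a false discovery rate for activation maps).

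**Interaction test.** This is Hotelling's T² on the four between-ROI contrasts, referred to F(4, 15). With group differences δ₁…δ₅ and mean δ̄, its non-centrality is λ = (n/2) × Σ(δⱼ − δ̄)² / (1 − ρ).

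**Levels test.** This is a t-test with 18 df on each participant's mean over ROIs. The SD of that mean is √[(1 + 4ρ)/5], and the non-centrality is δ̄ × √(n/2) / SD = δ̄ × 2.236 / SD.

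**Uniform shift of 1 SD.** Every δⱼ equals δ̄, so λ = 0 and the interaction rejects at exactly alpha. The same holds for any size of shift and any ρ. For the levels test:

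| ρ | SD of ROI mean | Non-centrality | Power, alpha 0.05 | Power, alpha 0.025 |
|---|---|---|---|---|
| 0.3 | 0.663 | 3.37 | 89% | 81% |
| 0.5 | 0.775 | 2.89 | 78% | 67% |
| 0.7 | 0.872 | 2.56 | 68% | 56% |

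Simulation gave the same picture within sampling error: 4.6 to 5.4% for the interaction over shifts of 0.5 to 1.5 SD, and 67 to 89% (alpha 0.05) or 54 to 82% (alpha 0.025) for the levels test at 1 SD.

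**Nearly uniform shift.** Take 1.2, 1.1, 1.0, 0.9 and 0.8 SD. Then Σ(δⱼ − δ̄)² = 0.04 + 0.01 + 0 + 0.01 + 0.04 = 0.10. At ρ = 0.5, λ = 5 × 0.10 / 0.5 = 1.0 and the interaction has 9% power. The mean shift is still 1, so the levels test keeps its 78%.

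**Shift of 1 SD in one ROI only.** Here δ̄ = 0.2 and Σ(δⱼ − δ̄)² = 0.64 + 4 × 0.04 = 0.80.

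| ρ | λ | Interaction, alpha 0.05 | Interaction, alpha 0.025 | Levels, alpha 0.05 |
|---|---|---|---|---|
| 0.3 | 5.71 | 34% | 23% | 10% |
| 0.5 | 8.00 | 46% | 33% | 9% |
| 0.7 | 13.33 | 71% | 57% | 8% |

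The two tests answer different parts of the hypothesis, and neither replaces the other.

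**Cue specificity.** Suppose users differ by 1.5 SD in one ROI, equally for cannabis and nature images, with an assumed cross-cue correlation of 0.5. In simulation the interaction on cannabis values alone rejects in 70 to 97% of trials. On cannabis-minus-nature values it rejects in 5%.

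**The case against.** Several points on the other side stand.

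- **The interaction is relevant.** The hypothesis speaks of regional activation and the analysis targets differing patterns. A reader might infer that the interaction is the wrong test and should be replaced. The one-ROI result shows otherwise.
- **Profile analysis ordinarily includes a levels test.** The method is sound and the text does not exclude that test. But it names none, ties no conclusion to one, and opens the ROI tests only through the interaction. This is a rule the protocol itself fixes, so it is not a detail left to a later plan.
- **Other routes exist.** A reader might infer that a uniform difference would leave no ROI information at all. The documents do not support that: percent BOLD in the ROIs is summarised descriptively without a gate, the Aim 2 GEE models include group, and section 2.0 adds exploratory whole-brain analyses. None of these carries the Aim 1 decision.
- **The nature control is not abandoned.** A reader might infer that it goes unused. Section 2.0 and Stimuli both plan the comparison, and the blurred baseline has its own stated purpose of controlling for non-specific visual stimulation. What holds is narrower: no test stated in General statistical methods uses the nature scenes.
- **A general response difference need not pass as a cue effect.** If it is equal across ROIs, the interaction cancels it. The false finding simulated above needs a difference that is uneven across ROIs. The levels test, however, is exposed to a global difference, so adding it makes the nature contrast more necessary.
- **The GLM wording.** Image Acquisition says the model is "to examine regional brain activation in response to photic stimulation and the semantic task". This study has no semantic task, so the phrase needs editing, but it has no bearing on the choice of test.

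**Conclusion.** The point holds. As written, the Aim 1 rule detects a user-control difference common to all ROIs only at the alpha rate, about 5%. That result is algebra and does not depend on the assumed effect, SD or correlation. The size of the loss does: for a uniform 1 SD shift a levels test on the same data would have about 68 to 89% power at alpha 0.05, or 56 to 81% at 0.025. These levels-test figures are for values before any nature subtraction. The missing nature contrast is a gap between the stated tests and the protocol's own design.

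This is a should-fix. The study is a pilot for feasibility whose key outcome is effect sizes, and no confirmatory decision rests on the Aim 1 p-value.

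**What to change.** In General statistical methods:

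1. Prespecify the group main effect (levels test) alongside the group-by-ROI interaction, with alpha split between them, for example 0.025 each. Do not use a hierarchy in which a non-significant levels test blocks the interaction.
2. Make the multiplicity-controlled ROI comparisons, and report ROI effect sizes, whatever the interaction shows.
3. Define the Aim 1 response as cannabis-minus-nature percent BOLD (and food-minus-nature for the food cues), or include cue as a within-subject factor.

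The reference to a semantic task in Image Acquisition can be corrected at the same time.

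**Cost.** Only analysis wording changes, since the nature runs are already planned. The split lowers the interaction's power for a 1 SD shift in one ROI from 34-71% to 23-57%. Subtraction multiplies the SD by √[2(1 − c)], where c is the cross-cue correlation, which the protocol does not give. With ρ = 0.5, alpha 0.025 and a uniform 1 SD difference for cannabis images only, levels-test power is 51% at c = 0.3, 67% at c = 0.5 and 89% at c = 0.7. The subtraction may therefore cost or gain power.

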**Script for telephone screening is attached as Appendix B.**

**Informed consent form for patients and controls is included in IRB application.**

1. **Study Procedures**

We plan to enroll 35 participants. The study components will consist of an initial phone screen with the participant to verify provisional inclusion criteria. For applicants meeting provisional inclusion criteria, a screening visit will be scheduled for Informed Consent, explanation of study procedures, screening with study instruments and interviews, and an opportunity for a practice session in the mock MRI scanner. For applicants meeting inclusion criteria following screening, a study visit will be scheduled, preferably within 2 weeks of the screening day.

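### For Aim 1, the effect sizes meant to power the R01 come from post-hoc comparisons run only after a significant interaction in 10 per group, so they are biased upward

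*Protocol*

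**What the plan says.** Under General statistical methods, Aim 1 is a multivariate profile analysis of percent BOLD change across ROIs, cannabis users against controls. Five ROIs are named as examples. The order of steps is explicit: "Given a statistically significant interaction effect from an overall profile analysis, post-hoc tests controlling the experiment-wise Type I error rate will be used" to find which ROIs drive the profile difference, "as well as the magnitude and direction of the specific component difference". The next sentence reads: "These effect sizes will be used for statistical powering estimates in the planning of subsequent RO1 research".

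The group size is given as "Given proposed group sizes of 10 participants (with no missing data), we expect to use parametric statistical analysis procedures". Power Estimates justifies it by custom ("we estimate 10 subjects per group as reasonable sample size as this group size is commonly well in fMRI pilot studies") and states the role of the estimates: "A key outcome of this study will be the calculation of effect sizes that will inform the powering of subsequent, larger studies". Study Procedures gives a different total: "We plan to enroll 35 participants", with no split by group.

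For Aim 2 (change after the two exercise conditions, GLM with GEE), the effect sizes are also sent to the R01, but no significant test is required first. The same section also promises descriptive summaries of BOLD change in the targeted ROIs, without any condition.

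**The concern.** In the Aim 1 text, the effect sizes designated for powering are the output of the conditional post-hoc step. In a small sample an estimate reaches significance mainly when chance has pushed it up, so the average of the estimates that pass exceeds the true value. The protocol mentions no confidence limit, shrinkage or minimum effect of interest to offset this.

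What is at stake is the pilot's declared purpose, which is to support the R01 application. If the R01 is sized on inflated Aim 1 effects, it will enrol too few participants to detect the real ones.

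**Working it through.** **Inputs from the protocol.** 10 per group (General statistical methods, Power Estimates); five example ROIs; 35 enrolled (Study Procedures). The 10 per group has no effect size, SD, alpha or power behind it, so there is no calculation to reproduce.

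**Assumptions, none stated in the protocol.** True standardised difference d from 0.3 to 1.0; two-sided alpha of 0.05, or 0.01 as Bonferroni for five ROIs (0.05 / 5); R01 sized for 80% power at two-sided 0.05.

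**Step 1: the smallest observed d that is significant.** d_min = t(1 − alpha/2, 18) × sqrt(2/10).
- alpha 0.05: 2.101 × 0.4472 = 0.94
- alpha 0.01: 2.878 × 0.4472 = 1.29

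**Step 2: inflation if only significant ROIs are carried forward.** Mean observed d among significant results in the right direction, divided by true d (two-sample t-test, 18 df, 400,000 simulated pilots per case):

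| True d | Power at 0.05 | Inflation at 0.05 | Inflation at 0.01 |
|---|---|---|---|
| 0.3 | 0.10 | 4.0x | 5.1x |
| 0.5 | 0.19 | 2.5x | 3.1x |
| 0.8 | 0.40 | 1.65x | 2.0x |
| 1.0 | 0.56 | 1.4x | 1.65x |

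Simulating both steps (Hotelling test of parallel profiles on five ROIs, inter-ROI correlation 0.3 to 0.7, one or two ROIs truly different, then Bonferroni post-hoc tests; 20,000 draws per scenario) gives 3.2x at d = 0.5 and 2.0x to 2.1x at d = 0.8. That agrees with the 0.01 column.

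**Step 3: inflation if only the interaction selects.** Same simulation, but keeping every truly different ROI once the interaction is significant: 1.3x to 1.85x at d = 0.5, 1.1x to 1.5x at 0.8, 1.1x to 1.4x at 1.0. With no selection at all the ratio is 1.03 to 1.06, which is ordinary small-sample bias.

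**Step 4: what this does to the R01.** Take true d = 0.5 and alpha 0.05. The mean significant d is about 1.24.
- Size planned on 1.24: 12 per group
- Size needed for 0.5: 64 per group
- Real power with 12 per group at d = 0.5: about 22%

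(These use the t distribution; the normal approximation gives 11 and 63.) If only the interaction selects, the planned size at d = 0.5 is 19 to 37 per group against 63, by the normal approximation. The shortfall is smaller but in the same direction.

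**Step 5: a larger pilot.** If the 35 enrolled split evenly, there are about 17 per group. Carrying forward only significant ROIs then gives 1.9x / 2.3x at d = 0.5 and 1.3x / 1.5x at d = 0.8 (alpha 0.05 / 0.01).

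**Step 6: does the small-sample correction cure it?** No. The Hedges factor is 1 − 3/(4 × 18 − 1) = 0.958. At d = 0.5 it lowers 2.48x only to 2.37x, because the bias comes from the selection.

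**The case against.** The strongest reply is that the text makes only the omnibus interaction an explicit condition. It does not say that magnitudes are kept for significant ROIs alone. On that reading the bias is the smaller one in Step 3, and an effect carried forward need not exceed 0.94. This stands, and it is why both ranges are given.

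Three stronger inferences are tempting, and the documents do not support them.
- A reader might infer a fixed inflation of two- to three-fold. That holds only for some assumed effects: about 0.5 to 0.8 if only Bonferroni-significant ROIs are kept. It is 4x to 5x at 0.3 and below 2x at 1.0.
- A reader might infer that a non-significant interaction leaves the pilot with no effect sizes. Aim 2 yields effect sizes with no stated condition, and the descriptive ROI summaries are unconditional. Only the Aim 1 effect sizes designated for powering would lack a stated source. That could well happen: in the Step 3 simulation the interaction was significant in 11% to 30% of pilots at d = 0.5.
- A reader might extend the bias to all effect sizes sent to the R01. The Aim 2 text gives no ground for that.

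It can also be said that unbiased Aim 1 effects could be computed from the descriptive summaries. They could, but the protocol names the conditional results as the source for powering.

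Finally, the harm falls on a later application that will choose its own sample size. Participant safety and this pilot's own tests are untouched, which lowers the severity.

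**Conclusion.** The point holds for Aim 1. The stated source of the R01 effect sizes is conditional on significance at 10 per group, and the bias is upward in every case computed. Its size depends on an assumed true effect and on which condition does the selecting: roughly 1.4x to 5.1x for d of 1.0 down to 0.3 if only significant ROIs are carried forward, and 1.1x to 1.9x for d of 0.5 to 1.0 if only the interaction selects. The mismatch between 35 enrolled and 10 per group leaves the relevant sample size uncertain, but about 17 per group reduces the bias without removing it. This should be fixed, because effect-size estimation is a key outcome of the pilot and the remedy is simple.

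**What to change.** In General statistical methods, replace the conditional source for Aim 1. State that the standardised group difference (Hedges-corrected) and its 95% CI will be reported for every prespecified ROI, whether or not the interaction or any post-hoc test is significant. State that R01 planning will use this full set together with the SDs, not the significant ROIs. The interaction and post-hoc tests can stay as inference.

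A rule that sizes the R01 on the lower 95% confidence limit would not serve. With 10 per group that limit is below zero for any observed d under 0.94 (an observed 0.5 gives −0.40 to 1.38), so it would often yield no sample size.

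The cost is analysis wording only, with no added participants or procedures. The R01 planning figure will be less favourable.
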